## Abstract

**Background:**

In the context of major trauma, the rate of wound infection in surgical incisions created during fracture fixation amongst patients with closed high-energy injuries is high. One of the factors which may reduce the risk of surgical site infection is the type of dressing applied over the closed incision. The WHIST trial evaluates the effects of negative-pressure wound therapy (NPWT) compared with standard dressings.

**Methods/design:**

The WHIST trial is a multicentre, parallel group, randomised controlled trial. The primary outcome is the rate of deep surgical site infection at 30 days after major trauma. Secondary outcomes are measured at 3 and 6 months post-randomisation and include the Disability Rating Index, the EuroQoL EQ-5D-5 L, the Doleur Neuropathique Questionnaire, a patient-reported scar assessment, and record of complications. The analysis approaches for the primary and secondary outcomes are described here, as are the descriptive statistics which will be reported. The full WHIST protocol has already been published.

**Discussion:**

This paper provides details of the planned statistical analyses for this trial and will reduce the risks of outcome reporting bias and data driven results.

**Trial registration:**

International Standard Randomised Controlled Trials database, ISRCTN12702354. Registered on 9 December 2015.

## Background

Major trauma is the leading cause of death in patients under 45 years and a significant cause of short- and long-term morbidity [1]. In the context of major trauma, the wounds associated with surgery to fractured limbs are notoriously difficult to manage. Even in closed high-energy injuries associated with major trauma, the rate of infection in surgical incisions created during fracture fixation remains high; tibial plateau fractures are associated with infection rates of up to 27% [2–6] while pilon fractures have an incidence of deep infection ranging from 5 to 40% [7–10]. If surgical site infection does occur, treatment frequently continues for years after the trauma with significant personal and societal costs [11].

One of the factors which may reduce the risk of surgical site infection in the surgical wounds of major trauma patients is the type of dressing applied over the closed incision at the completion of the operative procedure. Traditionally, the surgical incision is covered with an adhesive dressing or gauze maintained in place with a bandage to protect the wound from contamination from the outside environment. Negative-pressure wound therapy (NPWT) is an alternative form of dressing which may be applied to closed surgical incisions. In this treatment, an open-cell, solid foam overlies the incision and is covered with a semipermeable membrane. A sealed tube is used to connect the foam to a pump which creates a partial vacuum over the wound.

There has only been one randomised trial comparing standard wound dressing with NPWT for patients with closed surgical wounds following major trauma to the limbs [12]. This trial demonstrated a reduction in the rate of late/deep wound infections in patients treated with NPWT (9%) versus those treated with standard dressings (15%); however, the reduction was of borderline statistical significance (*p* = 0.049), and the study has since been criticised for methodological flaws [13]. In addition, a recent Cochrane review concluded that further trials regarding the effects of NPWT are required [13].

The WHIST trial is a large-scale, multicentre, parallel group, randomised controlled trial designed to compare the rates of deep infection in patients with major trauma requiring surgical incisions for the treatment of lower limb fractures treated with NPWT compared to those treated with standard wound dressings. The protocol paper for the WHIST trial has been published previously [14]; the aim of this paper is to report in detail the analysis plan as agreed by the trial steering committee in March 2018. This paper has been prepared according to the published guidelines on the content of statistical analysis plans [15].

## Methods and design

### Trial design

WHIST is a multicentre, two-arm, parallel-group, superiority randomised controlled trial designed to compare the rates of ‘deep infection’ in patients allocated to standard wound dressing versus those allocated to NPWT. Eligible patients are randomised on a 1:1 basis using minimisation to balance the two treatment groups by trial centre, open or closed fracture at presentation, and Injury Severity Score (ISS) ≤ 15 versus ISS ≥ 16. Neither participants nor their treating surgeons are blind to treatment allocation since wound dressings are clearly visible. The primary outcome is assessed at 30 days after randomisation with secondary outcomes assessed at baseline, 30 days, and 3 and 6 months after randomisation. Full details of the trial design, study population, and study procedures have been published previously [14].

The trial is registered with the International Standard Randomised Controlled Trials database, ISRCTN reference number ISRCTN12702354.

### Objectives

The primary objective of this trial is to quantify and draw inferences on differences in the rate of deep infection of the lower limb in the 30 days after major trauma between participants receiving standard dressings and those receiving NPWT. Secondary objectives include assessing differences between the same groups in disability, wound healing, quality of life, neuropathic pain, and the number and nature of complications experienced at 3 and 6 months post-randomisation.

### Outcomes

#### Primary outcome

The primary outcome for this study is the rate of deep infection; the Centre for Disease Control and Prevention (CDC) definition of a “deep surgical site infection”—a wound infection involving tissues deep to the skin that occurs within 30 days of injury [16]—is used. Since the trial began, the CDC definition of a deep surgical site infection has been modified to include wound infections occurring up to 90 days after injury if metal implants are used in the fracture fixation [17]. Although not all wounds associated with lower limb fracture surgery contain implants, this is the most common method of fixation and therefore we will incorporate this alternative definition of the primary outcome in a supplementary analysis to ensure the study can be utilised in future systematic reviews and meta-analyses.

#### Secondary outcomes

The secondary outcome measures, recorded at 3 and 6 months post-injury unless otherwise stated, are as follows:Disability Rating Index (DRI) [18]: a self-administered, 12-item visual analogue scale (VAS). Each item is scored from 0 (carry out task without difficulty) to 100 (not at all). Total scores are calculated as an average across all 12 items with higher scores indicating greater disability.Euroqol EQ-5D-5 L [19, 20]: a self-reported outcome measure consisting of five dimensions each with five possible responses which are converted to multi-attribute utility scores where 1 represents perfect health, 0 represents death, and scores less than 0 are possible. The EQ-5D-5 L also includes a 0–100 VAS recording overall health status with higher scores representing better health.Doleur Neuropathique Questionnaire (DN4) [21]: seven yes/no questions with total scores being the number of questions answered yes. Scores of 3 or greater are considered indicative of neuropathic pain.Patient-reported scar assessment using the patient scale from the Patient and Observer Scar Assessment Scale (POSAS) [22]: six questions each scored out of 10. The answers are summed to give an overall score out of 60 with higher scores indicating better healing. This scale is also measured at 30 days post-injury.Complications grouped into three categories: (i) local complications related to the injury or operation—this will include wound healing assessment at 30 days using photographs, signs of infection up to 6 months, and other local complications; (ii) systemic complications related to the injury or operation—this will include other related SAEs; and (iii) unrelated SAEs.

### Sample size

Only one previous randomised trial has compared NPWT to standard dressings for surgical incisions associated with major trauma to the lower limb [12]. This trial indicated that the rate of ‘late’ (deep) infection was reduced by 6%; from 15% in the standard treatment group to 9% in the NPWT group.

In the absence of a minimum clinically important difference for deep wound infection, we surveyed surgeons in the UK Orthopaedic Trauma Society who perform surgery for major trauma to the limbs (unpublished data, 2015). This survey showed that a 6% reduction in the rate of ‘deep infection’ would, universally, be sufficient to change clinical practice with regard to the choice of dressing. Therefore, assuming a reduction in the proportion of patients having a deep infection from 15% to 9%, 615 patients would be required in each group to provide 90% power at the 5% level (two-sided) when comparing two independent proportions. Previous experience in clinical trials of lower limb fracture surgery for major trauma indicates that up to 20% of the primary outcome data may be lost during the follow-up period due to death and loss to follow-up [23]; therefore, we propose to recruit 1540 patients in total for this trial (770 per arm).

### Statistical analysis

#### General analysis principles

Two analysis populations will be considered, the intent-to-treat (ITT) population and the per-protocol (PP) population. The ITT population will include all participants randomised with the exception of those who: (i) prospectively declined consent but were subsequently randomised in error; (ii) retrospectively declined consent and requested that all their data were removed; or (iii) withdrew and requested that all their data were removed. Participants will be analysed according to the group to which they were randomised. The PP population will be analysed according to the treatment they actually received. Participants with major protocol deviations or violations will be excluded from the PP population. Major protocol deviations are those who did not satisfy the eligibility criteria (for example their wound could not be closed primarily), those who did not receive the allocated treatment, and those for whom insufficient data are available on the primary outcome. The definition of the PP population will be finalised during a blinded analysis of the data prior to the primary analysis time point.

A significance level of 0.05 will be used throughout, and 95% confidence intervals will be reported. The primary conclusion of the trial will be based on the results from the primary analysis of the primary outcome. Sensitivity analyses of the primary outcome will be performed to assess whether these results are robust. All analyses of secondary outcomes will be considered as supporting the primary analysis, and conclusions of the trial will not be based on these outcomes.

All analyses will be carried out using appropriate, validated statistical software such as STATA [24] or R [25]. The relevant package and version number used for the analysis will be recorded and reported.

#### Descriptive analyses

The flow of participants through each stage of the trial, including the number of eligible individuals screened, randomised to each arm, receiving allocated treatment, and included in the primary analysis will be summarised using a CONSORT flow chart (Fig. 1). Reasons for ineligibility, loss to follow-up, and exclusion from the primary analysis will be summarised, as will the number of patients declining consent both prospectively and retrospectively.

**Fig. 1 Fig1:**
[figure not shown]
CONSORT flow diagram for participants in trial up to 6 months follow-up

The baseline comparability of the two randomised groups in terms of (i) minimisation factors, (ii) baseline characteristics (Table 1), (iii) operative procedure details (Table 2), and (iv) secondary outcomes at baseline will be presented. Numbers with percentages will be used to compare binary and categorical variables, and either means and standard deviations or medians and interquartile ranges will be used for continuous variables. There will be no tests of statistical significance nor confidence intervals for differences between the randomised groups.

**Table 1 Tab1:** Baseline characteristics

Baseline characteristic	Type	Levels or scale
Sex	Binary	Male; female
Age	Continuous	Years
BMI	Continuous	kg/m^2^
Marital status	Categorical	Single; separated; married/civil partner; living with a partner; divorced; widowed
Ethnicity	Categorical	White; Black Caribbean; Black African; Black other; Indian; Pakistani; Bangladeshi; Chinese; other
Training post school	Categorical	None; formal work qualification; college/university non-degree; degree from college/university
Employment status	Categorical	Full-time employed; part-time employed; self-employed; retired/looking after home/inactive; unpaid work; unemployed; full-time student
Mechanism of injury	Categorical	Low energy fall; high energy fall; road traffic accident; crush injury; contact sports injury; other
Any other injuries	Binary	Yes; no
Diagnosed with diabetes	Binary	Yes; no
Regular smoker	Binary	Yes; no
Alcohol consumption per week	Categorical	0–7 units; 8–14 units; 15–21 units; more than 21 units
Regular analgesia before injury	Binary	Yes; no
Other medication before injury	Binary	Yes; no

**Table 2 Tab2:** Operative procedure details

Operative procedure detail	Type	Level or scale
Lead surgeon grade	Categorical	Consultant; associate specialist; specialist trainee; other
Number of surgeons	Continuous	NA
Wound limb	Binary	Right; left
Wound location	Categorical	Hip; femur; patella; tibia; foot
How fixed	Categorical	Nail; plate and screws; wire/tension band wires; half-pin; fine pin; other
How closed	Categorical	Interrupted sutures; skin clips; subcuticular suture; any skin closure used; steristrips; glue; other
Intra-operative complications	Binary	Yes; no
If yes what	Categorical	Nerve injury; vascular injury; tendon injury; extension of fracture; other
Any other surgery	Binary	Yes; no
If yes what	Categorical	Head; chest; abdomen; pelvis; spine; upper limbs; ipsilateral limb; contralateral limb
Prophylactic antibiotics	Binary	Yes; no
Duration of operation	Continuous	Minutes

#### Loss to follow-up, withdrawals, and missing data

The numbers (and percentages) of losses to follow-up and withdrawals along with reasons for these will be reported by intervention arm at each time point. To ensure that differential losses do not occur between the two groups this will be tested using absolute risk differences (with 95% confidence intervals) and a chi-squared test. Any deaths and their causes will be reported separately.

The patterns of availability of data for primary and key secondary outcomes, from baseline to end of follow-up, will be summarised for the two treatment groups (as number and percentage of individuals missing). Reasons for missing-ness will also be presented, if known. Where appropriate, differentiation will be made between partially completed and fully missing outcome data. Two analysis datasets will be considered: (i) the available case dataset, consisting of all observed data; and (ii) the imputed dataset, where missing data are imputed. Missing data on the primary outcome will be imputed using a best case worst case analysis, considering the situation where all participants in the Standard dressing group with missing data are assumed to have a deep infection and all participants in the NPWT group with missing data are assumed not to have a deep infection and vice versa. Missing data on continuous outcomes will be imputed using multiple imputation (MI) under the missing at random (MAR) assumption. The suitability of the MAR assumption will be considered.

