#### Analysis of primary outcome

The numbers and percentages of ‘deep infections’ occurring up to 30 days post-randomisation in the two study intervention groups, NPWT and standard dressing, will be calculated. The rates of deep infection in the two study groups will be compared using a mixed effects logistic regression model. The model will include a random effect to account for any heterogeneity in the response due to recruitment centre. Fixed effects to adjust for open versus closed fractures, ISS level (≤ 15 vs ≥ 16), participant age, and participant gender will also be included. Participant age and gender are included in the model since there is evidence that older men have worse outcomes after major trauma. The result will be reported as an odds ratio (OR) with associated 95% confidence interval and *p* value for comparison between the two treatment groups. The unadjusted OR and associated 95% confidence interval will also be reported.

This analysis will be conducted for the ITT population using the available case dataset. As sensitivity analyses, the analysis will be repeated for: (i) the ITT population using an imputed dataset (best case worst case analysis); and (ii) the PP population using the available case dataset. In addition, a sensitivity analysis taking account of the competing risk of death [26] will be conducted if a sufficient number of deaths have occurred prior to 30 days, that is if more than 5% of participants have died prior to this time point.

If a significant treatment effect of NPWT is identified in the primary analysis, an exploratory subgroup analysis will be conducted to investigate whether this effect is moderated by the underlying risk level of the wound. This will be done by repeating the primary analysis and including wound location (above or below the knee) as a covariate. Wound location will be used as a proxy for wound risk level due to differences in soft-tissue cover; there being less soft-tissue cover below the knee.

The main analysis of the primary outcome (ITT population using the available case dataset) will be repeated using the alternative definition of ‘deep infection’, including infections occurring up to 90 days after injury. If any of the sensitivity analyses conducted for the primary endpoint (30 days) demonstrated substantially different results from the primary analysis, these analyses will be repeated for the rates of deep infection up to 90 days.

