## Trial status

Recruitment for the trial closed on 17 April 2018. In total 1548 patients from 24 study sites were recruited. Follow-up is currently ongoing and expected to finish in October 2018; the analysis of outcomes up to 6 months after randomisation will be conducted thereafter. The trial also includes long-term follow-up from 1 to 5 years and the analysis of these data will be reported separately.

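### The only sensitivity analysis for missing primary outcomes is a best/worst-case bound, which is uninformative at the plan's 20% loss allowance; a tipping-point analysis would fill the gap

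*SAP article*

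**What the plan says.** The SAP article, section Loss to follow-up, withdrawals, and missing data, gives one method for the primary outcome: "Missing data on the primary outcome will be imputed using a best case worst case analysis". In one scenario every missing standard-dressing patient counts as infected and every missing NPWT patient as not infected; the other scenario is the reverse. Multiple imputation under MAR is specified there for continuous outcomes only.

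The section Analysis of primary outcome makes the adjusted mixed-effects logistic model on available cases the main analysis. It lists three sensitivity analyses:
- best/worst-case imputation;
- the per-protocol population, again on available cases;
- a competing-risk analysis, only if more than 5% have died before 30 days.

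On the 90-day definition, the same section repeats the sensitivity analyses conditionally: "If any of the sensitivity analyses conducted for the primary endpoint (30 days) demonstrated substantially different results from the primary analysis".

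General analysis principles gives the purpose of the sensitivity analyses, which is to judge whether the primary result is robust. Sample size allows for the possibility that "up to 20% of the primary outcome data may be lost during the follow-up period due to death and loss to follow-up".

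**The concern.** Neither of the other two sensitivity analyses fills the role of a missing-data check. The per-protocol analysis excludes patients with insufficient primary outcome data, and the competing-risk analysis concerns deaths only. The robustness of the primary result to missing outcomes is therefore judged only by setting the missing patients' infection rate to 100% in one arm and 0% in the other, against planning rates of 9% to 15%.

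If the bounds span both significant benefit and significant harm whatever the data show, the reader learns only that some outcomes were missing. The question that matters goes unanswered: how different would the missing patients have to be before the conclusion changed?

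**Working it through.** **Inputs.** From Sample size: 15% versus 9%, "615 patients would be required in each group to provide 90% power at the 5% level (two-sided) when comparing two independent proportions", up to 20% lost, 770 per arm planned. From Trial status: "In total 1548 patients from 24 study sites were recruited", so about 774 per arm at 1:1. The 30-day missing share is not given, so it is varied from 1% to 20%, equal in both arms. An unadjusted comparison stands in for the mixed model. Odds ratios (OR) are NPWT versus standard, with Wald intervals and p-values.

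**Plan's own figure.** With mean rate 0.12:

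n = [1.96 √(2×0.12×0.88) + 1.2816 √(0.15×0.85 + 0.09×0.91)]² / 0.06² = 614.4, hence 615. Then 615/0.80 = 768.75, hence 769, rounded to 770. The plan's figures reproduce.

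**Scenario least favourable to NPWT.** With a share m missing per arm, the rates become 0.15(1−m) for standard and 0.09(1−m)+m for NPWT. The difference is

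0.15(1−m) − 0.09(1−m) − m = 0.06 − 1.06m,

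which is zero at m = 0.06/1.06 = 5.7%. The pooled rate is 0.12 + 0.38m. At m = 2.5%:

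z = 0.0335 / √(2×0.1295×0.8705/774) = 0.0335/0.01707 = 1.96,

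so significance is lost at about 2.5%, roughly 19 patients per arm. Significant reversal starts at about 9.1%.

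| Missing per arm | Standard | NPWT | Least favourable OR (95% CI), p | Most favourable OR |
|---|---|---|---|---|
| 1% | 14.85% | 9.91% | 0.63 (0.46–0.86), 0.003 | 0.52 |
| 2% | 14.70% | 10.82% | 0.70 (0.52–0.95), 0.023 | 0.48 |
| 3% | 14.55% | 11.73% | 0.78 (0.58–1.05), 0.10 | 0.45 |
| 5% | 14.25% | 13.55% | 0.94 (0.71–1.26), 0.69 | 0.39 |
| 10% | 13.50% | 18.10% | 1.42 (1.07–1.87), 0.013 | 0.29 |
| 20% | 12.00% | 27.20% | 2.74 (2.09–3.58), <0.001 | 0.16 |

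The rates shown are those in the least favourable scenario. With no missing data the OR is 0.56.

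**Sampling variation.** In 200,000 simulated trials per setting (770 per arm, true rates 15% and 9%), the share of significant available-case results that stayed significant in the least favourable scenario was 88% at 1% missing, 68% at 2%, 39% at 3%, 5% at 5%, and none at 10% or 20%.

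**Would an intermediate analysis discriminate?** Hold missing standard patients at 15% and multiply the infection odds in missing NPWT patients by d:

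q = 0.09d/(0.91 + 0.09d), NPWT rate P = 0.09(1−m) + mq.

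Treating the imputed counts as observed:
- 10% missing, d = 5: q = 0.331, P = 0.114, OR 0.73, p = 0.037.
- 20% missing, d = 2: q = 0.165, P = 0.105, OR 0.665, p = 0.008.
- 20% missing, d = 3: q = 0.229, P = 0.118, OR 0.76, p = 0.063.

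Those p-values are too small because they ignore imputation uncertainty. Rubin's total variance of P with many imputations is

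P(1−P)/N + m²q′²p(1−p)/[N(1−m)] + mq(1−q)/N, with p = 0.09 and q′ = d/(1−p+dp)²,

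and likewise for the standard arm with p = 0.15 and d = 1. Dividing each by [P(1−P)]² gives the logit scale. For 10% missing and d = 5 the two arms contribute 0.0164 and 0.0113, so the standard error is 0.166, z = ln(0.73)/0.166 = −1.89 and p = 0.06. At d = 4 (OR 0.70), p = 0.03. For 20% missing, p = 0.02 at d = 2 and 0.11 at d = 3.

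The tipping point is therefore about 4 to 5 times the odds at 10% missing, and between 2 and 3 times at 20%. The best/worst-case analysis reports significant harm in its least favourable scenario in both settings.

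**The case against.** Best/worst case is a transparent bound that needs no model, and a result that survives it is very secure. The 20% is an upper planning allowance, not an observed 30-day loss. The plan bases its conclusion on the primary analysis, reports missingness with reasons by arm, and tests for differential loss. No rule in it labels a result non-robust because the bounds disagree. All of this stands, and it limits the point to a supporting analysis.

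Several stronger readings are tempting but not supported:
- **That the bounds overturn any realistic result at about 3% missing.** For a design-sized effect only significance is lost there; the direction holds to about 5.7%. An observed 15% versus 7% stays significant to about 4.4% missing, and 15% versus 5% to about 6.1%. An exact null at 12% becomes significant in one scenario only from about 3.4%.
- **That no plausible analysis is planned.** When only the outcome is missing, the adjusted available-case logistic model is valid under MAR given its covariates. Multiple imputation under MAR alone would add mainly auxiliary information and would test much the same assumption.
- **That patients who die are set to infected.** Sample size counts death as a source of lost data, but the missing-data section does not say whether deaths enter the imputation. This is an ambiguity, not a stated rule.
- **That the 90-day trigger is a defect.** If the bounds nearly always meet it, the 90-day sensitivity analyses are nearly always run, which does no harm.

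**Conclusion.** The point holds in a limited form. Best/worst case is the only sensitivity analysis for missing primary outcomes. For a design-sized effect it loses significance at about 2.5% missing per arm. At the 20% allowance its two ends (OR about 0.16 and 2.74) are significant in opposite directions, so it cannot serve its stated purpose there. Below about 2% missing it can still confirm such an effect. The gap is the absence of any analysis between MAR and the extreme bounds.

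The figures assume equal missing shares in both arms, observed rates of 15% and 9%, and an unadjusted comparison. How much the point matters in practice depends on the 30-day missing share, which the document does not report. The primary estimate is not affected.

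**What to change.** In Loss to follow-up, withdrawals, and missing data, and in Analysis of primary outcome:
1. Add a prespecified tipping-point analysis of 30-day deep infection by delta-adjusted multiple imputation. Vary the infection odds in missing patients separately by arm, for example from 1 to 5 times the observed odds, with 1 in both arms as the MAR reference.
2. Name the imputation predictors from those already collected: the minimisation factors, age, sex, diabetes, smoking and wound location.
3. Keep best/worst case, described as the extreme corner of that grid.
4. State whether patients who died before 30 days enter the imputation.

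This is a cheap improvement: a paragraph of text, modest programming and no new data collection. Follow-up was still running when the article was written, so it could be fixed before the analysis. The downside is a few more sensitivity results to report.
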